## c. Village-level data

Village-level data were collected about usual water sources, sanitation, and other issues by key-informant interviews. Coverage data were collected following each MDA. In general, the data on numbers receiving treatment was provided by those administering treatment – either school personnel or community health workers. In some projects, such as in Kenya Sm1 and Sm2, MDA was carried out by the study team. In other places, such as in Cote d'Ivoire, the national program administered the MDA. Denominator data came from

a variety of sources, including governmental census reports, village leader estimates, and door-to-door surveys.

In SBT villages, coverage was recorded for SAC. In CWT villages, coverage values for both SAC and the entire population were requested.

In all studies except Cote d'Ivoire, Year 2 cost data were collected in a sample of at least 5 representative SBT villages in each study. In Cote d'Ivoire, data were collected in Year 3. In Sh2 and Sm2 studies, data were collected in at least 5 representative CWT villages as well. Data included information on personnel; transport; and consumables, materials, and services. Investigators were asked to capture program costs and not the costs of research.

Limited data are also available on snail quantities, species, and schistosomes population genetics from eight villages from Arm 1 and eight villages in Arm 6 in Tanzania.

**Because of variability in data capture, secondary analyses of costs and the influence of village-level and parasite strain factors are not included as part of this SAP. These analyses will be developed separately by the individual investigators.**

#### IV. SCORE UNIFORM DATASETS

SCORE used standardized approaches to data cleaning and creation of analytic data sets. Data were cleaned in country based on a series of checks provided by SCORE. "Clean" data were sent to SCORE for further assessment, and issues identified with the data (e.g., missing data, data that appeared to be out of range, etc.) were sent back to the country to be corrected to the extent possible. One value that appeared clearly wrong – a weight of 12 kg for a 9-year-old child – was re-coded as missing.

Rules employed in the SUDS datasets include:

- Individuals who did not have parasitological data recorded were entirely excluded from the datasets.
- Inclusion in the age groups: 5-8 years, 9-12 years, and adult was based on recoded ages, except for adults in some Kenya data who were documented to meet the 20-55 age requirement but did not have exact ages recorded. Mozambique enrolled many children with recorded ages outside the study requirements in the belief that these children were likely of appropriate ages for inclusion in the study. If the recorded age did not meet study criteria, these were classified as "Other."

Once clean, data were placed in the SCORE Uniform Data Set (SUDS) format, and returned to the country. Datasets for each study are stored separately. (Each country has only one study, except for Kenya, whose two studies (Sm1 and Sm2) are stored in individual datasets).

Each data set is available in SAS, Excel, and \*.csv formats, and is accompanied by the appropriate SUDS data dictionary. The data dictionary also includes metadata pages specific for each study site, indicating issues identified during data collection and cleaning that may need to be taken into account in analysis.

SUDS data dictionaries for Sh and Sm Gaining and Sustaining studies and Cohort studies are in Appendices E and F, respectively. The SUDS data dictionary for coverage is in Appendix G.

## V. DEFINITIONS OF PREVALENCE, INTENSITY, AND COVERAGE

The following definitions will be used for individual-level data:

- Individual mean eggs per gram (epg) (Sm studies):  $24 \times \text{total number of eggs found in all slides} / \text{number of slides examined}$ . Individual mean epg will be used for reporting, as it is the standardly used metric for infection intensity.
- Individual egg count (Sm studies):  $\text{Total number of eggs found in all slides examined} / \text{number of slides examined}$ . Individual egg count will be used for analysis, as epg does not have a continuous distribution. Note that some software packages may require individual egg count to be rounded prior to analysis. If the analysis requires integers, then the egg count used for formal statistical analysis should be  $6 \times \text{Total number of eggs found in all slides examined} / \text{number of slides examined}$ , rounded to the nearest whole number. If estimated counts are over 1,000 after adjustment for number of slides, they should be truncated at 1,000, as is common practice in schistosomiasis clinical research studies.
- Individual mean eggs per 10 ml (Sh studies):  $\text{Number of eggs found} \times 10 / \text{volume of urine filtered}$ . If estimated counts are over 1,000 after volume adjustment, they should be truncated at 1,000. Mean eggs per 10 ml will be used for both analysis and reporting, as this measure is both continuous and a standard metric. Note that some software packages may require mean eggs per 10 ml to be rounded prior to analysis, but this will only affect individuals with less than 10ml of urine filtered.
- Egg positive: a child will be deemed to be egg-positive if one or more eggs were found in any of the slides examined.

The following definitions will be used for reporting on cross-sectional and cohort studies:

- **Prevalence of *Schistosoma* infection:** Percentage of egg-positive children among the 9-12 year olds tested in each community each year.
- **Mean intensity of *Schistosoma* infection:** *Arithmetic* mean of individual mean epg or eggs per 10 ml among the 9-12 year-old children. Two values are to be reported:
  - i) Village-level intensity: This is the mean egg count for all tested 9-12 year-old subjects (including those with zero egg counts), which is a measure of community-level contamination potential.
  - ii) Individual-level intensity: This is the mean egg count among egg-positive subjects, which is an estimate of the intensity of infection among known active cases.
- **SBT coverage:** Numbers of school-age children treated / numbers of school-age children.
- **CWT coverage:** Numbers of people in the community treated / number of treatment-eligible people in the community.

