11. *Evaluate schistosomiasis prevalence and intensity at baseline and then annually.* The most important outcomes for the study relate to schistosomiasis prevalence and intensity in the population in all years in which MDA is conducted.

The following populations will be tested:

- In all studies: 100 children in the classes that include those 9-12 years of age. If there are more than 100 children in this age range, select children randomly for testing. For children in this age range in Sm communities, 3 stools will be examined. These prevalence and intensity evaluations will be done each year preceding MDA. (They will not be conducted in communities having a drug holiday.)
- In all studies: 100 first year students in the first and fifth years. For Sm1 and Sm2 studies, it is acceptable to examine 1 stool per child, except in communities doing subtle morbidity studies, where 3 stools per child will be collected. If samples for 100 first year students cannot be obtained, test as many as possible. Do not add age groups.
- In Sh2 and Sm2 studies: 50 adults ages 20-55 years from the community in the first and fifth years. For Sm2 studies, it is acceptable to examine 1 stool per adult, except in communities doing subtle morbidity studies, where 3 stools per adult will be collected. A variety of processes to identify these adults will be acceptable. A subgroup will work to articulate these. They could range from a random sample of adults identified through the census to a random selection of areas within the study village and random selection of adults from within those, to other options. Only one adult per

household should be selected, and pregnant women are eligible. SCORE does not require adults to be tested in Sh1 and Sm1 studies.

In Sh1 and Sh2 studies, a single mid-day urine should be tested, with eggs quantified and recorded separately for two 10-ml filtrations. In Sm1 and Sm2 studies, 2 slides per stool should be examined using Kato-Katz. It is acceptable to collect stools for Sm1 and Sm2 studies but defer reading them until later.

12. *Conduct MDA and record serious adverse experiences (SAE).* Praziquantel (PZQ) will be provided as a single dose of 40 mg/kg, using a dose pole, using the approach defined by the study arm. Normal PZQ treatment exclusion criteria apply. MDA will not be provided during drug holidays.

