#### a. Individual-level data in Gaining and Sustaining studies

Parasitological data on *Schistosoma* infection among children ages 9-12 were collected prior to each MDA and a year following the last treatment. No data were collected in villages during a holiday year.

In the Sm studies, duplicate Kato-Katz slides were made from each of three daily stool samples from each individual, and the number of eggs found in each slide was recorded. In the Sh studies, 10 ml of urine from a single well-stirred urine sample for each individual was filtered twice, and each of these two filtrations was examined under the microscope; the number of eggs found in each slide and the corresponding volume of urine filtered was recorded.

Parasitological data were also collected in Years 1, 3, and 5 on children in the first-year class and in Years 1 and 5 on adults (see Appendix D). However, given that data on these populations do not represent the

primary end-points of the SCORE treatment studies, and that the data collected on them are much more limited than that for 9-12 year olds, they will not be reported as primary end-points.

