**Figure 3. Intensity categories, by Arm, by Year.**

This is a stacked bar chart, showing low, medium, and high intensity infections, by Arm, for Years 1-5.

Intensity categories are defined as:

- Sm: Low=1-99 epg, Medium=100-399 epg, high $\geq$ 400 epg
- Sh: Low 1-50 eggs/10 ml, high $\geq$ 51 eggs/10 ml

A supplemental table including the numbers used to make the chart should be available should modelers or other analysts want to use the exact data.

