## V. DEFINITIONS OF PREVALENCE, INTENSITY, AND COVERAGE

The following definitions will be used for individual-level data:

- Individual mean eggs per 10 ml (Sh studies): Number of eggs found \* 10 / volume of urine filtered. If estimated counts are over 1,000 after volume adjustment, they should be truncated at 1,000. Mean eggs per 10 ml will be used for both analysis and reporting, as this measure is both continuous and a standard metric. Note that some software packages may require mean eggs per 10 ml to be rounded prior to analysis, but this will only affect individuals with less than 10ml of urine filtered.
- Egg positive: a child will be deemed to be egg-positive if one or more eggs were found in any of the slides examined.

The following definitions will be used for reporting on cross-sectional studies:

- **Prevalence of *Schistosoma* infection:** Percentage of egg-positive children among the 9-12 year olds tested in each community each year.
- **Mean intensity of *Schistosoma* infection:** *Arithmetic* mean of individual mean eggs per 10 ml among the 9-12 year-old children. Two values are to be reported:
  - i) Village-level intensity: This is the mean egg count for all tested 9-12 year-old subjects (including those with zero egg counts), which is a measure of community-level contamination potential.
  - ii) Individual-level intensity: This is the mean egg count among egg-positive subjects, which is an estimate of the intensity of infection among known active cases.

- **SBT coverage:** Numbers of school-age children treated / numbers of school-age children.
- **CWT coverage:** Numbers of people in the community treated / number of treatment-eligible people in the community.

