### Figure 3. Intensity categories, by Arm, by Year.

This is a stacked bar chart, showing low, medium, and high intensity infections, by Arm, for Years 1-5, and each study separately. Intensity categories are defined as:

- Sh: Low 1-50 eggs/10 ml, high  $\geq 51$  eggs/10 ml

A supplemental table including the numbers used to make the chart should be available should modelers or other analysts want to use the exact data.

Table 4. Comparisons of prevalence and intensity at Year 5 among arms.

This table describes the primary outcomes.

|                         | Unadjusted prevalence model estimate (CI) | Adjusted prevalence model estimate (CI) | Unadjusted intensity ratio (CI) | Adjusted intensity ratio (CI) |
|-------------------------|-------------------------------------------|-----------------------------------------|---------------------------------|-------------------------------|
| Study A: Arm 1 v. Arm 2 |                                           |                                         |                                 |                               |
| Study B: Arm 1 v. Arm 2 |                                           |                                         |                                 |                               |
| Study C: Arm 1 v. Arm 2 |                                           |                                         |                                 |                               |

*General approach to analysis:* The general approach is to use mixed models to estimate differences between the arms in year 5 only, analyzing each study separately. We will report unadjusted estimates – with just village, study group and arm fitted in the model – and adjusted estimates – where sex and age are also included in the model. The mixed model will implicitly weight for any villages that were not able to sample 100 9-12 year old children.

ICC will be calculated using mixed models in the primary analysis.

All models will be based on individual level data on 9-12 year old children only.

*Sample code:* The following codes are provided as examples.

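### In both SAPs, S. haematobium intensity moves in half-egg steps, so the limit placed on rounding is false and the lightest infections fall outside the Figure 3 bands (minor)

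*Combined protocol and SAP*

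**What the plan says.** **Collection.** The protocol (Study components, item 11) requires that "a single mid-day urine should be tested, with eggs quantified and recorded separately for two 10-ml filtrations". Section III.a of the main SAP, which covers Mozambique, says the urine "was filtered twice, and each of these two filtrations was examined under the microscope" and that "the number of eggs found in each slide and the corresponding volume of urine filtered was recorded". The Niger SAP, section III.a, has the same rule.

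**Definition.** Section V of both SAPs defines individual intensity as "Number of eggs found \* 10 / volume of urine filtered", truncated at 1,000. It adds: "Mean eggs per 10 ml will be used for both analysis and reporting". If software needs whole numbers, the value may be "rounded prior to analysis, but this will only affect individuals with less than 10ml of urine filtered". The same section counts a child as egg-positive if any slide shows one or more eggs. For S. mansoni, section V of the main SAP gives an integer rule (6 times eggs per slide, rounded). S. haematobium has no counterpart.

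**Categories.** Figure 3 in both SAPs is a stacked bar chart "showing low, medium, and high intensity infections, by Arm, for Years 1-5". The bands are "Sh: Low 1-50 eggs/10 ml" and high from 51 upwards. No medium band is defined for S. haematobium. A supplemental table with the underlying numbers is to be kept for modelers and other analysts.

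**The concern.** The rounding sentence and the printed bands fit a whole-number scale. That is the scale of one 10-ml filtration per child, not of the two that the documents require.

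Two things follow if the text is applied literally:

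- A child with a single egg in 20 ml counts towards prevalence but has no place in Figure 3 or its supplemental table. The category totals then cannot match the infected counts in Table 3, and users of the supplemental table inherit the shortfall.
- An analyst whose software needs integers is told that rounding is harmless for fully sampled children, and is given no rule for ties. Rounding 0.5 gives 1 or 0 depending on the package. Both SAPs exist to make analyses consistent and both allow other packages, so this choice should not be left to the software.

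**Working it through.** **Step 1: the plan's own statement.** With volume V ml in all and T eggs in all, intensity = 10T / V.

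- V = 10: intensity = T, always whole. The SAP sentence is reproduced only under this reading, one 10-ml filtration per child.
- V = 20, the complete sample: intensity = T / 2. Of the totals 1 to 200, the 100 odd ones are fractional. Averaging two 10-ml readings gives the same values.
- V = 15: 134 of the totals 1 to 200 are fractional.
- V = 5: intensity = 2T, always whole. So the sentence is also inexact below 10 ml.

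**Step 2: the bands.** Each value was checked against 0, 1-50 and 51 or more.

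- V = 20: T = 1 gives 0.5 and T = 101 gives 50.5. Neither is in a band.
- V = 15: T = 1 gives 0.67 and T = 76 gives 50.67. Neither is in a band.

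**Step 3: how many children (illustration).** The documents give no egg-count distribution. I assumed one negative binomial per group and 20 ml for every child. Inputs from Table S6 are prevalence p (infected / tested) and community-level mean m per 10 ml, so the mean total is μ = 2m. Solve (1 + μ/k)^(-k) = 1 - p for k. Then P(1 egg) = k × μ / (k + μ) × (1 - p).

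Example, B1 at Year 5: p = 839 / 3,621 = 0.2317; μ = 2 × 3.61 = 7.22; k = 0.0537. P(1 egg) = 0.0537 × 7.22 / 7.2737 × 0.7683 = 0.0410. As a share of positives this is 0.0410 / 0.2317 = 17.7%, or about 148 of 839.

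**Step 4: effect of rounding on the arm mean.** Rounding halves up adds 0.5 for each odd total, so the relative shift is 0.5 × P(odd) / m. For B1, the odd share of positives is 56.0%, so P(odd) = 0.560 × 0.2317 = 0.130 and the shift is 0.5 × 0.130 / 3.61 = +1.8%. Rounding halves to even sends 0.5 to 0 and 1.5 to 2, so the shifts partly cancel.

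| Year 5 group | Infected / tested | Mean per 10 ml | One egg, share of positives | Odd total, share of positives | Mean, half up | Mean, half to even |
|---|---|---|---|---|---|---|
| A1 | 22 / 3,710 | 0.13 | 18.1% | 56.3% | +1.3% | -0.3% |
| A2 | 9 / 3,648 | 0.05 | 18.4% | 56.4% | +1.4% | -0.4% |
| B1 | 839 / 3,621 | 3.61 | 17.7% | 56.0% | +1.8% | -0.4% |
| B2 | 503 / 3,740 | 1.39 | 20.6% | 57.1% | +2.8% | -0.8% |
| C x1 | 425 / 3,689 | 1.37 | 20.0% | 56.9% | +2.4% | -0.7% |
| C x2 | 392 / 3,724 | 2.18 | 17.6% | 56.1% | +1.4% | -0.3% |

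The pooled baseline groups give one-egg shares of 16.1% to 20.9% and shifts between -0.7% and +2.6%. The two Group A SHSS subgroups at baseline, with 21 and 28 positives, give one-egg shares of 31% and 35%. The 50.5 gap holds about 0.1% of positives.

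**Step 5: effect on an arm ratio, half up.** B2 / B1: 1.028 / 1.018 = 1.010, a rise of about 1%. C x2 / C x1: 1.014 / 1.024 = 0.990, a fall of about 1%.

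**The case against.** **No primary result is shown to be wrong.** A reader might infer that the primary analysis is compromised. The documents do not support that. Prevalence uses the any-egg rule and is untouched. The intensity measure is otherwise analysed unrounded, and nothing shows that any S. haematobium analysis rounded it. If one did, the ratio would move by about 1% in this illustration, against an interval such as 0.74 to 3.21 for SSSS vs. CCCC in Mozambique (Table S3). This stands.

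**Infected children are not counted as uninfected.** A reader might infer that 0.5 is read as no infection. The egg-positive rule forbids that. The child is left unclassified, and a sensible analyst would probably put it in the low band. This stands too, but neither SAP says so. Only in a model fitted after rounding halves to even would such a child enter as a zero.

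**There is no systematic bias between arms.** A reader might infer that the loss favours one treatment frequency. The unclassified share is higher in B2 than in B1 but lower in C x2 than in C x1, so no direction follows.

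**The size is soft.** It rests on one distribution per group fitted to two rounded figures, ignores village clustering and assumes 20 ml for everyone. Table S6 also reports individual-level means almost equal to the community-level means (3.61 and 3.61 for B1 at Year 5), although section V defines the former among positives only, so the inputs deserve caution. This stands: the percentages are illustrative. The arithmetic of steps 1 and 2 does not depend on them.

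**The data dictionary (Appendix E) may settle the coding.** It was not available for this review. Even if it does, the rounding sentence and the bands would still need to agree with it.

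**Conclusion.** The concern holds as an error in wording with a limited effect. Under the documents' own collection rule and formula, the statement about who is affected by rounding is false, and the S. haematobium bands leave 0.5 and 50.5 unclassified. These two facts need no assumption beyond two 10-ml filtrations entering the formula, which is what the documents describe.

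The size is conditional on the negative binomial model and on 20 ml per child: about 16-21% of egg-positives unclassified in the pooled Niger groups, and up to about 35% in small subgroups. For Mozambique the documents give ratios only, so no estimate is possible. S. mansoni results are not involved. Because the effect falls on a descriptive figure, its supplemental table and a conditional rounding note, severity is minor.

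**What to change.** In both SAPs:

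1. Delete the sentence limiting the effect of rounding. Where integers are needed, use 2 × mean eggs per 10 ml, rounded, after the 1,000 eggs per 10 ml truncation. This mirrors the S. mansoni 6x rule. At 20 ml it returns the actual egg total (up to the truncation), and the factor 2 is common to all arms, so the intensity ratio keeps its scale.
2. Define the Figure 3 bands for S. haematobium without a gap and with one cut-off: none = 0; low = above 0 and below 51; high = 51 or more eggs per 10 ml. A value of 50.5 is then low.
3. Remove the medium band for S. haematobium.
4. Require low plus high to equal the egg-positive count in Table 3 for each arm in the years the two outputs share.

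The cost is a few lines of text and a recode. Egg counts and volumes are already recorded for each filtration, so no new data are needed.

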## VI. STUDY QUESTIONS AND END-POINTS OF INTEREST FOR GAINING AND SUSTAINING STUDIES

The following study questions and endpoints of interest are derived directly from the objectives as stated in the original, harmonized SCORE protocol.

### a. Key research questions for Gaining and Sustaining studies

The primary research questions are:

- 1a. Does the final (Year 5) prevalence of schistosomiasis among children age 9-12 differ by Study Arm?
- 1b. Does the final (Year 5) mean intensity of Sm or Sh infection among all children aged 9-12 differ by study arm?

More specifically, the planned analysis will involve a series of arm-to-arm comparisons, prioritized according to what questions are likely to be most important for decision-makers. Because there is risk of “false discovery” of statistically significant association when multiple comparisons are made (Type I error), the number of comparisons formally tested will be restricted. In both studies, the focus of analysis will be on comparison of the current standard of care with alternative treatment strategies in decreasing order of priority. P value cutoffs will not be adjusted. However, this potential limitation of the analyses will be included in the discussion of results, and interpretation will be guided by the strength of the arm-specific effects.

In Sm1 and Sh1 areas, the standard for morbidity control in relatively low-prevalence areas is annual SBT (Arm 1). Instituting “holidays” is hypothesized to lessen the impact of a treatment program on prevalence and intensity. This yields the following comparisons in priority order:

1. Because alternate years of SBT and Holidays would be the easiest to institute, the first comparison in Sm1 should be between **Arm 1 and Arm 3**.
2. Subsequently, we will compare **Arm 1 and Arm 2**.

For high prevalence communities, the standard for schistosomiasis control is annual SBT, as conducted in Arm 4 of the Gaining and Sustaining studies. Instituting CWT may increase the impact of treatment on local prevalence and intensity of *Schistosoma* infections. Under this consideration, the following comparisons are to be considered for the Sm2 and Sh2 trials:

1. Because annual SBT is the standard, the first comparison should be between **Arm 1 and Arm 4**.
2. Subsequently, we will compare **Arm 1 and Arm 2, Arm 1 and Arm 3, Arm 4 and Arm 5, and Arm 4 and Arm 6**.

The original statistical analysis plan for evaluating the Gaining and Sustaining studies is found in Appendix H.

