### Research questions and study components

#### Primary question

What strategy for mass drug administration (MDA) provides the best balance in terms of cost and reductions in prevalence and intensity of *S. haematobium* or *S. mansoni* in school-aged children after 4 years of intervention? Specifically, these studies are designed to answer the questions:

- **Sh1:** In communities/villages with *S. haematobium* baseline prevalence 10-24% by filtration or 5-20% by dipstick, what combination of annual school-based treatment (SBT) and drug holidays yields the best outcomes for the lowest cost?
- **Sh2:** In communities/villages with *S. haematobium* baseline prevalence  $\geq 25\%$  by filtration or  $\geq 21\%$  by dipstick,
  - Is there a difference between doing community-wide treatment (CWT) in Years 1 and 2 vs. SBT in those years in terms of parasitologic outcomes after four years?

- After the first two years, what additional benefit accrues from annual MDA vs. providing a drug holiday, and at what cost?
- What is the impact of alternating years of MDA and drug holidays?
- **Sm1:** In communities/villages with *S. mansoni* baseline prevalence 10-24% by 3 stool examinations with 2 Kato-Katz slides per stool per child, what combination of annual SBT and drug holidays yields the best outcomes for the lowest cost?
- **Sm2:** In communities/villages with *S. mansoni* baseline prevalence  $\geq 25\%$  by 3 stool examinations with 2 Kato-Katz slides per stool per child,
  - Is there a difference between doing CWT in Years 1 and 2 vs. SBT in those years in terms of parasitologic outcomes after four years?
  - After the first two years, what additional benefit accrues from annual MDA vs. providing a drug holiday, and at what cost?
  - What is the impact of alternating years of MDA and drug holidays?

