#### Unadjusted prevalence

The evaluation of unadjusted prevalence uses a binomial GEE with logit link function. Village\_ID is treated as the repeated subject, and we assume compound symmetry within a village. 'Lsmestimate' is used to test the pre-specified differences between arms.

```
ods trace off;
proc genmod data=allyears descending;
  where Study_Year = 5;
  class Study_Arm Village_ID / param=glm;
  model Sh = Study_Arm / dist=bin link=logit ;
  repeated subject=Village_ID / type=cs;
  lsmeans Study_Arm / cl;
  lsestimate Study_Arm "arm 2 vs. arm 1" -1 1 0 0 0 0 / cl;
  lsestimate Study_Arm "arm 3 vs. arm 1" -1 0 1 0 0 0 / cl;
  lsestimate Study_Arm "arm 4 vs. arm 1" -1 0 0 1 0 0 / cl;
  lsestimate Study_Arm "arm 5 vs. arm 1" -1 0 0 0 1 0 / cl;
  lsestimate Study_Arm "arm 6 vs. arm 1" -1 0 0 0 0 1 / cl;

  lsestimate Study_Arm "arm 3 vs. arm 2" 0 -1 1 0 0 0 / cl;
  lsestimate Study_Arm "arm 4 vs. arm 2" 0 -1 0 1 0 0 / cl;
  lsestimate Study_Arm "arm 5 vs. arm 2" 0 -1 0 0 1 0 / cl;
  lsestimate Study_Arm "arm 6 vs. arm 2" 0 -1 0 0 0 1 / cl;

  lsestimate Study_Arm "arm 4 vs. arm 3" 0 0 -1 1 0 0 / cl;
  lsestimate Study_Arm "arm 5 vs. arm 3" 0 0 -1 0 1 0 / cl;
  lsestimate Study_Arm "arm 6 vs. arm 3" 0 0 -1 0 0 1 / cl;

  lsestimate Study_Arm "arm 5 vs. arm 4" 0 0 0 -1 1 0 / cl;
  lsestimate Study_Arm "arm 6 vs. arm 4" 0 0 0 -1 0 1 / cl;

  lsestimate Study_Arm "arm 6 vs. arm 5" 0 0 0 0 -1 1 / cl;
estimate "O.R. arm 2 vs. arm 1" Study_Arm -1 1 0 0 0 0 / exp cl;
run;
```

Adjusted prevalence

The code is the same as for unadjusted prevalence, but with age, sex, and a weighting for village size added to the model.

villweight of individual = 1/# samples collected in village

```
ods trace off;
proc genmod data=allyears descending;
  where Study_Year = 5;
  class Study_Arm Village_ID Sex Age / param=glm;
  model Sh = Study_Arm Sex Age / dist=bin link=logit ;
  repeated subject=Village_ID / type=cs;
  weight villweight ;
  lsmeans Study_Arm / cl;
run;
```

ICC of prevalence

```
/*macro*/
%macro icc_bin(data, cluster, outcome, out, m, stval=%str(), pred=%str());
proc nlmixed data=&data.;
  parms b0=0 &stval. var1=1;
  eta = exp(b0 + &pred. r);
  pred = eta / (1+eta);
  model &outcome. ~ binary(pred);
  random r ~ normal(0,var1) subject=&cluster.;
  estimate 'ICC' var1/(var1 + (constant('PI')**2)/3);
  estimate 'Deff' 1 + (&m.-1) * (var1/(var1 + (constant('PI')**2)/3));
  ods output AdditionalEstimates=&out.;
run;

data &out.;
  set &out.;

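### No listed Sm2/Sh2 contrast isolates the protocol's first primary sub-question (CWT versus SBT in Years 1 and 2), and the sample code's 15 pairs conflict with the SAP's own list of five

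*Combined protocol and SAP*

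**What the plan says.** The protocol, under Primary question, puts this first among the Sm2 sub-questions: "Is there a difference between doing CWT in Years 1 and 2 vs. SBT in those years in terms of parasitologic outcomes after four years". Sh2 has the same question, opening "Is there a difference between doing community-wide treatment (CWT) in Years 1 and 2 vs. SBT in those years". Two further sub-questions follow, on drug holidays after the first two years and on alternating years of treatment.

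Section VI of the main SAP says its questions are "derived directly from the objectives as stated in the original, harmonized SCORE protocol". For Sm2/Sh2, section VI.a ranks Arm 1 v Arm 4 first and then lists "Arm 1 and Arm 2, Arm 1 and Arm 3, Arm 4 and Arm 5, and Arm 4 and Arm 6". The Table 4 shell, which the SAP says describes the primary outcomes, has exactly these five rows. VI.a also says that "the number of comparisons formally tested will be restricted" and that p-value cutoffs will not be adjusted.

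Under Unadjusted prevalence in section VI.b, the SAP says the contrast statement "is used to test the pre-specified differences between arms". The code beneath it contains 5+4+3+2+1 = 15 such lines, one for every pair of the six arms.

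**The concern.** Two of the three sub-questions have listed contrasts: Arm 1 v 3 and Arm 4 v 5 address holidays, and Arm 4 v 6 addresses alternation. The first sub-question has none of its own. Nothing in the SAP says it was dropped or ranked lower, and the statement that the questions come directly from the protocol suggests otherwise. A trial that keeps to the list produces no estimate with an interval for a question its protocol calls primary.

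The second issue concerns formal testing. With no p-value adjustment, limiting the number of tests is the SAP's only procedural guard against false positives. A code block that applies the pre-specified label to every pair blurs which results have that standing.

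**Working it through.** **Which years each pair separates.** The arm sequences come from SAP section I: Arm 1 cccc, Arm 2 ccss, Arm 3 cchh, Arm 4 ssss, Arm 5 sshh, Arm 6 shsh.

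| Pair | Sequences | Years that differ | In VI.a and Table 4 |
|---|---|---|---|
| 1 v 4 | cccc / ssss | 1, 2, 3, 4 | yes |
| 1 v 2 | cccc / ccss | 3, 4 | yes |
| 1 v 3 | cccc / cchh | 3, 4 | yes |
| 4 v 5 | ssss / sshh | 3, 4 | yes |
| 4 v 6 | ssss / shsh | 2, 4 | yes |
| 2 v 4 | ccss / ssss | 1, 2 | no |
| 3 v 5 | cchh / sshh | 1, 2 | no |

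Of the 15 possible pairs, only the last two differ in Years 1 and 2 alone. The Table 3 shell labels Arm 3 as cshh. Under that label Arm 3 v 5 would differ in Year 1 only, and Arm 2 v 4 would be the sole isolating pair. The gap in the five listed contrasts is there under either label.

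**What the reported tables allow.** S2 and S3 report only the five pairs. Point estimates can be chained from the adjusted prevalence ratios:
- Tanzania: 2 v 4 = 1.05/1.09 = 0.96; 3 v 5 = 1.45/(1.09 × 1.33) = 1.00.
- Mozambique: 2 v 4 = 1.08/1.01 = 1.07; 3 v 5 = 1.45/(1.01 × 1.73) = 0.83.

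Chaining works as a check in Kenya (S1): 4 v 2 = 0.73/0.59 = 1.24 against 1.25 printed, and 5 v 3 = 0.73 × 1.49/1.19 = 0.91 against 0.91 printed. Intervals cannot be chained. With independent arms, each published variance is the sum of two arm variances, and five sums do not determine six arm variances.

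**What the design can give, using Kenya S1.** SE on the log scale = ln(upper/lower)/3.92.
- SSSS v CCSS 1.25 (0.68, 2.27): SE = 0.308. Inverted, early CWT v early SBT = 0.80.
- SSHH v CCHH 0.91 (0.62, 1.35): SE = 0.199. Inverted = 1.10.
- Mean log ratio = (−0.223 + 0.094)/2 = −0.064. SE = 0.5 × √(0.308² + 0.199²) = 0.183. Pooled ratio 0.94 (0.66, 1.34).
- Arm 1 v 4, 0.73 (0.42, 1.28): SE = 0.284. The pooled SE is 1 − 0.183/0.284 = 36% smaller.

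The two pairs use disjoint sets of villages, so they are treated as independent.

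**False positives.** The SAP gives no numeric alpha, so two-sided 0.05 is assumed, with six independent arm estimates of equal variance and no true differences. Simulation gives the chance of at least one false positive per outcome: 19.5% for the listed five; 22.6% with the pooled contrast added; 25.9% with the pooled contrast and both components; 36.5% for all 15 pairs (36.6% from the studentized range).

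**Bold results outside the list.** S1 bolds four prevalence ratios. SHSH v SSSS (Arm 4 v 6) is listed; CCHH, SSHH and SHSH, each v CCSS, are not. S4 is an Sm1 study, for which VI.a lists Arm 1 v 3 and Arm 1 v 2. Its one bold result, SHSH v SSHH, is neither.

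**The case against.** The SAP ranks comparisons by their use to decision-makers, centres them on the standard of care and keeps the number small. On that view Arm 1 v 4 is a deliberate choice. It does bear on CWT versus SBT, so a reader who infers that the list ignores the subject goes too far: the contrast covers Years 1 and 2 but mixes them with Years 3 and 4. What remains is that the SAP claims direct derivation from the protocol and does not say the narrower question was set aside.

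The code point is also limited. A reader might infer that the SAP plans 15 formal tests. The documents do not support that: the code is offered as an example, it is one of four model blocks, the other three request arm means only, and Table 4 keeps to five rows. A reader might likewise infer that Kenya broke the plan or reported pairs that were never pre-specified. The preface calls the SAP a minimum and encourages exploratory analyses, the text above the code gives all 15 pairs the pre-specified label, and Appendix H (the original analysis plan) was not available to check. The lack of adjustment is openly stated as a limitation. What stands is the inconsistency between text and code, and the missing exploratory label in S1 and S4.

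The Kenya figures are a weak demonstration of effect. SAP section VIII says Kenya's Year 1 CWT was less intense than SBT because schools were not used as venues. The two components also point in opposite directions (0.80 and 1.10), so 0.94 should not be read as evidence of no difference.

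**Conclusion.** The point holds in this form: no contrast in VI.a or Table 4 isolates CWT versus SBT in Years 1 and 2, and two of the three Study 2 trials report no interval for that question. This rests on the section I sequences and, for the five listed pairs, does not depend on how the Arm 3 label is settled. The use of Arm 3 v 5 as an isolating pair does depend on it.

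The design can address the question with four arms, nominally 50 v 50 villages. The 36% smaller SE in Kenya compares a four-arm contrast with a two-arm contrast of a different estimand. Equal-variance arms alone would give 1 − 1/√2 = 29%, so it should not be presented as an efficiency gain on the same question.

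The multiplicity half is a matter of labelling and consistency: a list of five beside one example block of 15, and four bold results across S1 and S4 that fall outside the lists. The false-positive rates depend on the assumed 0.05 and equal arm variances.

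**What to change.** - Add to VI.a and Table 4, for Sm2/Sh2, the contrast Arms 2+3 v Arms 4+5 (coefficients 0 1 1 −1 −1 0, divisor 2), with a stated place in the priority order. Show Arm 2 v 4 and Arm 3 v 5 beneath it as components, since they may differ in direction.
- State that the contrast was added after results had been tabulated.
- Before using Arm 3 in it, reconcile the two labels, cshh in the Table 3 shell and cchh in section I.
- State the scale. The sample model has a logit link and so yields an odds ratio, whereas S1 to S3 report prevalence ratios.
- Cut the sample code to the listed contrasts, or label the remaining pairs exploratory. Present the unlisted pairs in S1 and S4 as exploratory, without bold.
- Attach the section VIII caveat on Year 1 CWT to any Kenya estimate.

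The cost is a few lines of text and code and a re-run on existing data. The downside is one more formal contrast plus two components, which under the assumptions above raises the chance of a false positive per outcome from about 20% to about 23% (pooled contrast only) or 26% (with components tested).
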